## Abstract

In the United Kingdom, there are acknowledged short comings in allergy care provision for patients seen in primary care. There is a lack of allergy training for healthcare professionals and this leads to inappropriate referrals to the limited number of allergy specialists. The primary aims of this study are to assess the feasibility of delivering and evaluating a new nurse-led allergy service in primary care, measured by recruitment, retention and quality of life. This is a single arm feasibility trial in which up to 250 participants referred to the nurse-led allergy clinic will receive the intervention and complete 6–12 weeks follow-up before being referred back to their usual care. Primary outcomes for this study will be establishment of clinics, recruitment and retention rates, and estimates of change in disease-specific quality of life measures. Secondary outcomes will be acceptability of the new service to participants/carers and healthcare professionals. A sample of participants and professional stakeholders will take part in more in-depth semi-structured qualitative interviews. Data from this feasibility trial will be used to inform plans for a pilot randomised controlled trial of nurse-led allergy clinics.

## Introduction

The incidence and prevalence of allergic diseases has increased substantially over recent decades, and the United Kingdom has one of the highest rates of allergy in the western world.^1^ Allergic conditions affect approximately one in three people in Scotland at some point in their lives^2^ and the prevalence is thought to be even higher in children and young people, with an estimated 50% of the population now affected.^3^ Allergic conditions cost the UK’s national health services over £1 billion per annum.^4^

The term allergy covers a broad range of clinical conditions that share a common pathophysiology. The most common conditions and those responsible for the greatest healthcare utilisation include atopic eczema/dermatitis (henceforth atopic eczema), food allergy, asthma, allergic rhinitis, allergic conjunctivitis, urticaria and anaphylaxis. The majority of cases of allergy in the United Kingdom are managed within primary care.^5^ Specialist allergy care provision is patchy, but where it exists, evidence suggests that there are often unnecessary referrals to secondary care for conditions that could be dealt with in primary care settings.^5^ This in turn reflects important gaps in undergraduate and postgraduate training of general practitioners (GPs).^6^ There have been a number of national calls and initiatives aimed at improving allergy care provision in the United Kingdom.^7–9^

Jutel et al.^10^ have demonstrated that, given the very large numbers of people now affected by allergic conditions, expansion of allergy services delivered within ‘specialist settings’ is not a viable proposition. Rather, they suggest that there is a need to develop provision of allergy care within community settings. A report by the Children’s and Young People’s Allergy Network Scotland in 2013 found that, across Scotland, primary care practitioners did not feel they have the skills or knowledge to provide good quality allergy care, especially around diagnostic testing for allergy, and the ability to interpret the results.^11^

An earlier pilot primary care-based allergy service in England, run by a specialist allergy nurse and a GP with a special interest in respiratory disease and allergy, showed that a primary care intervention for allergy could effectively deal with the majority of cases of allergy seen in primary care, resulting in a reduction in inappropriate referrals into secondary care, an increase in self-supported care for patients and a saving in costs.^12^ These data however come from an uncontrolled study and therefore need to be interpreted with caution. A more recent study by Smith et al.^13^ found that a large percentage of referrals, which would have otherwise have been seen in secondary care, could adequately be dealt with in primary care by a practitioner with a specialist interest in allergy. Findings from a recent systematic review support the need for alternative models of allergy care provision.^14^ Systematic reviews of disease-specific nurse-led clinics have shown high levels of patient satisfaction; however, there remains a need for experimental trials to improve the level of evidence.^15,16^ In response to these findings, we are proposing a novel allergy service intervention that is nurse-led and primary care-based to improve the patient pathway and access to early allergy diagnosis and management.

The primary aims of this trial are to assess the feasibility of delivering and evaluating a nurse-led allergy clinic in a primary care setting in Scotland and to estimate the impact on disease-specific quality of life in patients referred to the service. The secondary aim is to measure the acceptability of the service to patient/carers and healthcare professionals (HCPs).

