## Methods

### Design

This is a feasibility trial of a single group assigned to a nurse-led allergy clinic in primary care. The trial was registered on ClinicalTrials.gov reference NCT03826953 on 1 February 2019 (https://clinicaltrials.gov/ct2/show/NCT03826953?term=NCT03826953&rank=1).

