### Eligibility criteria

The inclusion criteria are:Children aged <36 months with suspected food allergy.Children aged <36 months with moderate-to-severe atopic eczema not responding to standard treatment.Children and young people up to 16 years of age with suspected allergic rhinitis symptoms are not responsive to a combination of oral antihistamines and nasal steroids.Young people and adults (from 16 years of age) with a history of anaphylaxis or suspected anaphylaxis.Able to give informed consent.

The exclusion criteria are:

Children aged <36 months with suspected or confirmed non-IgE-mediated food allergy presenting primarily with gastrointestinal symptoms.Single urticarial reactions without obvious triggers.Non-allergic chronic urticaria.Drug allergy.Well-controlled allergic rhinitis, asthma or atopic eczema.Mild-to-moderate atopic eczema without any obvious allergic trigger.Localised insect sting reactions.Unable to give informed consent.

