### Outcome measures

This feasibility trial focuses on the ability to set up a new service in primary care, with a novel ‘hub and spoke’ referral model for patients with allergic disease. Prior to a pilot randomised controlled trial, it is important to assess the ability to recruit patients via this new service, and establish recruitment and retention rates and questionnaire response rates for future sample size estimates. The primary outcomes are:Recruitment of practices to facilitate establishing the new service and make referrals.Referral and consultation rates for nurse-led allergy clinic and retention rates.The change in disease-specific quality of life questionnaires between baseline and 6–12 weeks post intervention.

The following disease-specific quality of life questionnaires will be completed at baseline prior to the clinical intervention and at 6–12 weeks post intervention by telephone or email, and face to face for those patients who require a follow-up clinic appointment.Dermatology ○ Infants’ Dermatitis Quality Of Life Index^18^Allergic rhinitis○ Mini Rhinitis Quality of Life Questionnaire^19^Food allergy and anaphylaxis○ Food Allergy Quality of Life Questionnaire – Parent Form (children aged 0–12)^20^○ Food Allergy Quality of Life Questionnaire – Teenager Form (13–17 years)^21^○ Food Allergy Quality of Life Questionnaire – Adult form^22^

The secondary outcomes are:Patient satisfaction, measured immediately post intervention and 6–12 weeks post intervention by questionnaire.Referring HCP satisfaction measured after 1 year of the start of the nurse-led allergy clinics by questionnaire.Costs incurred by patients/carers.

A subset of referring HCPs, practice managers and patients/carers will be invited to take part in a semi-structured interview to gain in-depth insight into the feasibility of setting up and referring to the clinic, and to explore expectations and experiences of attending the nurse-led primary care allergy clinic.

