### Descriptive analysis

We will describe the number of practices approached to act as hubs and spokes and the number recruited. The characteristics of referring practices in terms of number of patients referred, practice list size and deprivation score will be reported. For patients we will describe the number approached and recruited, age, sex and referring condition. We will report the retention rate for follow-up. For disease-specific quality of life, the difference in the disease-specific quality of life score at baseline and post intervention will be descriptively compared without any formal statistical testing. Patient and professional satisfaction with the service will be reported. Costs (such as travel and time off work) incurred by the patients/carers will be reported.

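### A primary aim is to estimate the service's impact on quality of life, but a single-group before-after change cannot separate that impact from other causes of change

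*Protocol article*

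**What the plan says.** The Introduction gives two primary aims: to assess the feasibility of delivering and evaluating the clinic, and "to estimate the impact on disease-specific quality of life in patients referred to the service".

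Other sections fix what the data can support:

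- **Design:** "This is a feasibility trial of a single group assigned to a nurse-led allergy clinic in primary care".
- **Outcome measures** lists as the third primary outcome "The change in disease-specific quality of life questionnaires between baseline and 6–12 weeks post intervention".
- **Abstract** words the same outcome as "estimates of change in disease-specific quality of life measures", and names quality of life as one of the measures of feasibility.
- **Eligibility criteria** admit "Children aged <36 months with moderate-to-severe atopic eczema not responding to standard treatment". They also admit patients up to 16 years whose rhinitis has not responded to antihistamines plus nasal steroids, and exclude well-controlled rhinitis, asthma or eczema. The other two referral groups, suspected food allergy under 36 months and a history or suspicion of anaphylaxis from age 16, are not defined by current symptom control.
- **Descriptive analysis:** "the difference in the disease-specific quality of life score at baseline and post intervention will be descriptively compared without any formal statistical testing".

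Of the earlier English primary care pilot, the Introduction itself says: "These data however come from an uncontrolled study and therefore need to be interpreted with caution".

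**The concern.** Impact is a causal word. It asks how patients fared compared with how they would have fared without the clinic. One group measured twice holds no information on the second half of that comparison.

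Anything else that moves scores over 6–12 weeks enters the same number. Natural course and season apply to every referral group. For eczema and rhinitis there is a further reason to expect improvement. These patients are referred when treatment is not working, and patients picked at a bad point tend to score better next time whatever is done.

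At stake is what may be concluded on a primary outcome. A favourable change reported under an aim worded as impact invites the reading that the clinic caused it.

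**Working it through.** **1. Is there a plan figure to reproduce?** No. The target of about 250 with completed follow-up rests on available time and resources and on an English pilot that recruited 141 patients in 9 months. The article gives no effect size, SD, significance level or power, so there is no derivation to check.

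**2. Do the sections agree?** The Introduction aims at impact. The Abstract and Outcome measures define the outcome as change. Design gives one group. Change can be measured in one group; impact cannot be identified from it. The aim therefore exceeds both the design and the stated outcome.

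**3. How large could regression to the mean be?** All inputs here are assumptions, because the article gives no correlation and no score distribution. Take a normally distributed score, select the worst share p at baseline, and suppose the service has no effect.

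- Mean excess of those selected, in SDs: λ = φ(c)/p, where c is the cut-off and φ the normal density.
- Expected apparent improvement: (1 − ρ) × λ, where ρ is the baseline/follow-up correlation.

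| Share selected | λ | ρ = 0.5 | ρ = 0.6 | ρ = 0.7 | ρ = 0.8 |
|---|---|---|---|---|---|
| worst 75% | 0.42 | 0.21 | 0.17 | 0.13 | 0.08 |
| worst 50% | 0.80 | 0.40 | 0.32 | 0.24 | 0.16 |
| worst 25% | 1.27 | 0.64 | 0.51 | 0.38 | 0.25 |

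The range is 0.08–0.64 SD of the baseline score in the unselected population.

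**4. Would more patients help?** No. The 95% half-width of a mean change is about 1.96/√n in SDs of change: 0.36 at n = 30, 0.22 at n = 83 and 0.12 at n = 250. The first two are assumed numbers per questionnaire, since the article gives no split. A larger n narrows the interval around the biased value and leaves the bias as it is. These half-widths and the figures in step 3 are in different SD units, so they should not be subtracted from one another.

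**5. What if the change were later used as an effect size?** The article does not propose this. Suppose the observed change is 0.5 SD, of which 0.2 SD is bias. Per arm, n = 2(1.96 + 1.28)²/d².

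- Planned on d = 0.5 at 90% power: 85 per arm.
- Needed for d = 0.3: 234 per arm.
- Power of 85 per arm at d = 0.3: 0.3 × √(85/2) − 1.96 ≈ 0, so about 50%.

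With 0.3 SD of bias (true d = 0.2), 526 per arm are needed and power at 85 is about 26%.

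**The case against.** The best defence is that this is a feasibility study that behaves like one. It plans no test, words the outcome as change in two places, shows awareness of the limits of uncontrolled data, and leads to a randomised pilot. On that view only one word is out of line. This stands in part: the analysis needs no correction. But the word sits in a primary aim and decides how a primary outcome will be read. It is a statement that the design contradicts, so the brevity of an article does not explain it.

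Several stronger readings are tempting, and the article does not support them:

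- **A reader might infer that paired change, its SD and an interval are not planned.** The outcome is already defined as a change, and the analysis as a difference in score. Ruling out tests does not rule out SDs or intervals, and an article commonly leaves such detail to the full protocol or analysis plan.
- **A reader might infer that the study fails to supply what the next trial needs.** Outcome measures says its purpose is to "establish recruitment and retention rates and questionnaire response rates for future sample size estimates". The descriptive analysis covers numbers approached and recruited, and retention. The next study is a randomised pilot, which could itself supply between-arm variability. No section says the change will be an effect size.
- **A reader might infer that dropout will distort the comparison.** No section plans to set all recruits at baseline against responders at follow-up.
- **A reader might infer that all patients are selected on poor control.** That fits two of the four referral groups. The other two are served by three of the five questionnaires.
- **A reader might infer that the authors repeat the aim they criticise.** The findings they credit to the pilot concern how cases were handled, referrals, self-supported care and costs, not quality of life.

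The regression model is also open to challenge. Selection is by the referring clinician on treatment response, not by a cut-off on the questionnaire. Baseline is completed later, at the clinic appointment, so some regression may already have happened. The figures are therefore illustrative only.

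**Conclusion.** The point holds in a limited form: the stated primary aim of estimating impact cannot be met by a single-group before-after change, and it claims more than the outcome wording elsewhere in the article. This conclusion rests on the text alone and needs no assumption.

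The size does need assumptions. With ρ of 0.5–0.8 and selection of the worst 25–75% on the baseline score, regression to the mean alone could give 0.08–0.64 SD of apparent improvement, and only in the eczema and rhinitis groups. Natural course and season add an amount, in either direction, that the document gives no means to quantify. The harm to a later trial's sample size is conditional on a use of the change that the article does not announce.

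The aim should be corrected. The target of about 250, the choice of outcomes and the absence of significance tests are not in question.

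**What to change.** In the Introduction, replace the second primary aim with: *to describe within-participant change in each disease-specific quality of life questionnaire, without attributing it to the service*. Add one sentence under Descriptive analysis: *this change will not be used as the effect size for a later randomised trial*.

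A helpful addition, not a charged omission: for each questionnaire, in participants with both scores, report n, the mean paired change with its 95% confidence interval, and the SD of the change. No test is needed.

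The cost is the wording of one aim, one sentence and, if wanted, a few table columns. Recruitment and data collection are unaffected, and the article reports recruitment as still open, so the change can precede the results. The downside is a less ambitious stated aim.

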## Discussion

At the time of submission, we have recruited two hub practices who are receiving referrals from 21 of the 37 spoke practices, and one practice which is hosting a clinic for their own patients. There have been 265 referrals to the service, and 214 have been seen in the nurse-led clinic. Recruitment started in July 2017 and will continue until January 2020, when it is anticipated we will have reached our target sample size of 250 patients who have completed study follow-up.

## Methods

### Design

This is a feasibility trial of a single group assigned to a nurse-led allergy clinic in primary care. The trial was registered on ClinicalTrials.gov reference NCT03826953 on 1 February 2019 (https://clinicaltrials.gov/ct2/show/NCT03826953?term=NCT03826953&rank=1).

### Setting

Nurse-led allergy clinics are being established in the South West and South East localities of the Edinburgh Health and Social Care Partnership, Scotland.

### Ethical approval

South East Scotland Research Ethics committee approval was obtained (REC ref: 17/SS/0057).

### Recruitment of practices

A hub and spoke model was chosen for this trial, where hub practices act as the host for the nurse-led allergy clinic and spokes are the practices that can refer patients to these hubs. Eight general practices in the Edinburgh Health and Social Care Partnership newly formed south-east area cluster were approached by email to be hubs. This newly established cluster group has 20 general practices serving an estimated population of 134,000 patients, with a range of patient demographics. Two practices expressed an interest and were visited by the allergy nurse to explain the requirements for hosting the clinics. One practice agreed to operate as a hub practice, accepting referrals from spoke practices in the cluster, and the other agreed to host the clinics, but accepting only internal referrals. Subsequently, a third hub practice was recruited in the south-west area of Edinburgh with 17 practices acting as spokes serving an estimated population of 135,000 patients. Locality managers distributed study information packs to all practices in their cluster, and this was then followed up with an email to individual clinicians detailing the inclusion criteria for referrals, and a referral proforma. Regular emails are sent out reminding clinicians of the nurse-led allergy service.

### Recruitment of participants

All adults, young people and children who fit the eligibility criteria from the spoke practices can be referred to the nurse-led allergy clinic. Referrals are accepted from all HCPs who manage patients with allergies, including GPs, practice nurses and health visitors. The HCP will select the appropriate patients for referral, using an inclusion criteria checklist, and ask if they wish to attend the allergy clinic, advising patients and their carers that the nurse-led allergy clinic is part of a research study. On attendance at the clinic, patients/patient’s guardian are advised that they will need to provide written consent to take part in the study. If the patient does not wish to take part in the research project, they will be seen by their HCP as usual.

### Eligibility criteria

The inclusion criteria are:Children aged <36 months with suspected food allergy.Children aged <36 months with moderate-to-severe atopic eczema not responding to standard treatment.Children and young people up to 16 years of age with suspected allergic rhinitis symptoms are not responsive to a combination of oral antihistamines and nasal steroids.Young people and adults (from 16 years of age) with a history of anaphylaxis or suspected anaphylaxis.Able to give informed consent.

The exclusion criteria are:

Children aged <36 months with suspected or confirmed non-IgE-mediated food allergy presenting primarily with gastrointestinal symptoms.Single urticarial reactions without obvious triggers.Non-allergic chronic urticaria.Drug allergy.Well-controlled allergic rhinitis, asthma or atopic eczema.Mild-to-moderate atopic eczema without any obvious allergic trigger.Localised insect sting reactions.Unable to give informed consent.

### The intervention

The intervention is a nurse-led allergy service in primary care. The nurses have a postgraduate qualification in allergy and extensive experience of secondary care allergy clinics and are supported when necessary by a team of specialist services, including paediatric and adult allergy, dermatology, ear, nose and throat, respiratory, and ophthalmology. Referring HCPs are asked to complete a referral proforma and a referral sheet for each eligible patient, which is sent via secure National Health Service (NHS) email to the allergy nurse. Referrals are triaged by the allergy nurse according to the inclusion/exclusion criteria, and allocated an appointment by phone and letter/email. The ~45-min appointment includes an explanation of the study, taking written consent, and completion of baseline questionnaires assessing disease-specific quality of life and costs incurred by the patients/carers (see outcome measures below). The nurse then completes an allergy-focused history and clinical examination. Following this, the nurse will carry out investigations such as skin prick testing, give advice (written and oral) to support the management of allergies, including demonstration of medical devices (e.g. adrenaline auto-injectors, inhalers) and, if required, recommend medication(s). A letter summarising the consultation is then sent to the referring HCP including details of the medication to prescribe and the rationale for prescribing these items. The participants are then discharged back to the care of their referring HCP once they have seen the allergy nurse and have a diagnosis confirmed or refuted (see Fig. 1).

**Fig. 1 Fig1:**
[figure not shown]
Referral process into the nurse-led allergy clinic.

If, on examination, the allergy nurse feels the participant has multiple severe allergies or requires specialist hospital-based assessment, the participant will be advised that they will require referral onto secondary care (Fig. 2). Where appropriate, the allergy nurse will refer participants directly to specialists within secondary care. Where the local policy will not support nurse-led referrals, the nurse practitioner will make recommendations to the GP for the referral of the participant to the appropriate specialist services. Participants who have been seen in secondary care will be referred back to their usual HCP for long-term management. Long-term clinical follow-up will not be offered; some short-term follow-up may, however, be offered if deemed appropriate. All participants will return to their usual HCP for follow-up and long-term management.

